## Background

Knee osteoarthritis (OA) is the most common joint disorder, and the lifetime risk of developing symptomatic knee OA has been estimated to be around 45% [1,2]. Many patients present with unicompartmental knee OA, which is generally caused by a mechanical problem and may lead to knee malalignment [3]. Knee malalignment is a determinant of load distribution, and is associated with OA progression [4].

Alterations in the mechanical stresses on the knee joint tissues improves symptoms and reduces the risk of developing radiographic knee OA [5]. Valgus-producing high tibial osteotomy (HTO) does correct varus malalignment and is an accepted treatment for medial unicompartmental knee OA in active patients [6]. Aim of the HTO procedure is to offload the medial compartment by overcorrecting the varus malalignment to 2-6° of valgus [7-11].

The two most commonly used surgical techniques for HTO are lateral closing wedge HTO (LCW) and medial opening wedge HTO (MOW) with internal fixation, which has gained popularity in recent years. In both techniques the goal is to achieve and maintain adequate correction of malalignment of the knee joint. In the lateral closing wedge technique a wedge of bone with the base on the lateral side is removed from the proximal tibia, producing valgus. A fibular osteotomy or release of the proximal tibiofibular joint is necessary. After LCW, lateral tibial metaphyseal bone loss may occur and can lead to considerable lateral overhang of the tibial plateau, producing changes in tibiocondylar offset. MOW does not cause any bone loss but needs stable plate fixation with possible tibial slope changes, medial collateral ligament tightening and patella baja [12]. There are no differences between LCW and MOW in frequency and type of complications [13].

A relatively new HTO technique, the combined valgus-producing high tibial osteotomy (CWO), claims to include the advantages of both the LCW and the MOW techniques for HTO. This HTO modification avoids metaphyseal tibial bone loss, decreasing transposition of the tibial condyle and shortening of the patellar tendon after osteotomy, even in cases of great correction [14]. The aim of this prospective randomized trial (RCT) is to compare LCW with CWO in patients eligible for HTO who have varus alignment up to 12°. Hypothesis is that the CWO technique will achieve more accurate overcorrection of varus malalignment with fewer anatomical changes of the proximal tibia after one year.

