### Interventions

After randomization patients will undergo either a CWO HTO or a LCW HTO; all patients will be operated on by one of two orthopedic surgeons, both experienced in applying the two techniques so there will be no bias. Preoperative the wedge-correction is calculated aiming on 4° overcorrection.

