### Main study parameter/endpoint

Primary outcome measure is the accuracy and preservation correction of the technique, defined by achievement of an overcorrection of 4° valgus one year after surgery as measured by the hip-knee-ankle (HKA) angle. The continuous differences in achievement of a valgus overcorrection and the deviation from 4° valgus will be determined, as well as dichotomous outcome and achievement of a 0-6° valgus alignment .

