### Study procedures

Preoperatively as well as six weeks, six months and one year postoperatively, patients will visit the outpatient clinic. Routine physical examination will be performed by the orthopedic surgeon.

Primary outcome measure–achievement of an overcorrection of 4° valgus alignment / hip-knee-ankle angle (HKA, in degrees)–will be measured after one year on a whole-leg radiograph (WLR) standing on one leg. The continuous differences in achievement of a valgus overcorrection and the deviation from 4° valgus are determined. A dichotomous outcome is achievement of a 2-6° valgus alignment.

Secondary outcome measures, posterior tibial slope (Moore-Harvey and Dejour-Bonin), patellar height (Insall-Salvati and Caton Index) and difference in leg length (cm) one year after surgery will be obtained. Pain severity (VAS; range 0–10), knee function and quality of life (KOOS), and walking distance (km) six weeks, three months, six months and one year after surgery will also be obtained.

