### Sample size calculation

The sample size was calculated based on an expected increase of the success rate from 60% in the closed wedge HTO to 85% in the combined wedge HTO. A successful operative result is defined as achievement of a 2-6° valgus alignment. To detect such a difference with α= 0.05 and a power of 80%, we need to include 50 patients in each study group. To adjust for possible loss to follow-up, a total of 110 patients will be included in the study.

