### Statistics

All data will be analyzed according to an intention-to-treat principle, implying that all patients who are randomized will be included in the analyses, and that they will be analyzed according to the group to which they were allocated. For those patients who will be lost to follow-up or will be re-operated during follow-up, the last available measurement or the last measurement will be forwarded (Last Value Carried Forward technique).

A multivariable linear regression method will be used to analyze the impact of LCW versus CWO HTO on postoperative alignment, posterior tibial slope, patellar height, leg length, VAS, KOOS, walking distance and patients with adverse events at the one-year follow-up. A multivariable logistic regression method will be used for the dichotomous outcome measures. Gender, age and baseline values for HKA angle, VAS knee, KOOS, walking distance, medial osteoarthritis more than joint space loss alone, and concurrent OA of the lateral compartment will be considered as possible confounders and are included in the regression models only if they change the relationship between dependent variable and type of HTO by at least 10%. The SPSS program will be used for the statistical analyses and a p-value of 0.05 is considered statistically significant.

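### The linear regression is assigned to postoperative alignment, not to absolute deviation from 4°, so the continuous primary analysis compares mean angles rather than accuracy

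*Protocol article*

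**What the plan says.** The Background states the hypothesis in terms of accuracy: "Hypothesis is that the CWO technique will achieve more accurate overcorrection of varus malalignment". The Main study parameter/endpoint section uses the same construct: "Primary outcome measure is the accuracy and preservation correction of the technique". Both arms share one target, since under Interventions "Preoperative the wedge-correction is calculated aiming on 4° overcorrection" applies to either technique.

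For the continuous form of the primary outcome, the endpoint section says "The continuous differences in achievement of a valgus overcorrection and the deviation from 4° valgus will be determined", and Study procedures repeats it: "The continuous differences in achievement of a valgus overcorrection and the deviation from 4° valgus are determined". Two quantities are therefore listed, the overcorrection reached and the deviation from 4°. Neither section says whether the deviation is signed or absolute.

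The Statistics section assigns the models: "A multivariable linear regression method will be used to analyze the impact of LCW versus CWO HTO on postoperative alignment", followed by the secondary outcomes. Deviation from 4° is not in that list. Dichotomous outcomes go to logistic regression. The sample size rests on the dichotomous form: "expected increase of the success rate from 60% in the closed wedge HTO to 85% in the combined wedge HTO", where "A successful operative result is defined as achievement of a 2-6° valgus alignment".

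**The concern.** Alignment is measured as the HKA angle in degrees. A treatment coefficient from a linear regression of that angle is a difference in mean angle, and over- and undercorrections within an arm cancel. Accuracy is closeness to 4°, which is a different quantity. Adding the deviation does not help if it is signed: HKA − 4 is HKA minus a constant, so the treatment coefficient, its standard error and its p-value are unchanged.

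Two errors are possible. If the techniques differ in scatter but share a mean, the regression tends to show nothing although one is more accurate. If the means differ, a significant coefficient does not say which technique is more accurate. LCW at 4° with CWO at 5.5°, and LCW at 2.5° with CWO at 4°, both give a CWO-minus-LCW coefficient of +1.5°. With equal scatter they lead to opposite conclusions on accuracy.

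**Working it through.** **Inputs from the protocol.** Success 60% (LCW) and 85% (CWO); success means 2-6° valgus, i.e. within 2° of 4°; α = 0.05; power 80%; 50 per group; common target 4°.

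**Assumptions, not in the protocol.** HKA is normal in each arm; α is two-sided; both means are 4° in the base case, varied below. The protocol gives no SD for HKA.

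**1. The plan's own figure.** For two proportions, two-sided, pooled variance under the null, with mean proportion 0.725:

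n = [1.960·√(2·0.725·0.275) + 0.842·√(0.60·0.40 + 0.85·0.15)]² / 0.25² = 48.9, so 49 per arm.

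The stated 50 is reproduced; power at 50 per arm is 0.81.

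**2. SDs implied by the success rates.** With mean 4°, P(|HKA − 4| ≤ 2) = 2Φ(2/SD) − 1.

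- LCW: 60% gives SD = 2/z(0.80) = 2/0.842 = 2.38°.
- CWO: 85% gives SD = 2/z(0.925) = 2/1.440 = 1.39°.

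**3. Mean absolute deviation.** SD·√(2/π): 1.90° for LCW and 1.11° for CWO, a difference of 0.79°. The SD of the absolute deviation is SD·√(1 − 2/π): 1.43° and 0.84°. The standard error of the difference at 50 per arm is √((1.43² + 0.84²)/50) = 0.235, and 0.79/0.235 is about 3.4, which is far above 1.96.

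**4. Power with both means at 4°** (20,000 simulated trials, 50 per arm, two-sample t-tests; Wald logistic or chi-square for the range):

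| Outcome | Rejections |
|---|---|
| HKA angle | 5.2% |
| HKA − 4 (signed) | 5.2% |
| \|HKA − 4\| | 92.8% |
| Within 2-6° | 80% (Wald), 81% (chi-square) |

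**5. LCW mean allowed to drift, its success rate held at 60%, CWO at 4°:**

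| LCW mean | LCW SD | Power, HKA angle | Power, \|HKA − 4\| |
|---|---|---|---|
| 3.5° | 2.32° | 25% | 93% |
| 3.0° | 2.14° | 79% | 93% |
| 2.5° | 1.67° | 99.8% | 92% |

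Hand check at 3.0°: the standard error is √((2.14² + 1.39²)/50) = 0.36; 1.0/0.36 = 2.77; Φ(2.77 − 1.96) is about 0.79.

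**6. Equal accuracy, different means.** Illustrative values: means 3° and 5°, SD 2° in both arms. By symmetry about 4°, |HKA − 4| has the same distribution in both arms. The standard error for the angle is √(4/50 + 4/50) = 0.40, and 2/0.40 = 5. The angle comparison rejects in more than 99% of trials and the absolute deviation in about 5%, the nominal rate.

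**The case against.** **The text does not say signed.** A reader might infer that the plan specifies a signed analysis. It does not. The list in Statistics uses short labels: tibial slope and patellar height each stand for two measures defined elsewhere, so postoperative alignment may also be meant to cover the deviation. A signed deviation listed beside the angle would be redundant, which suggests that the authors had distance from 4° in mind. This stands as a plausible reading of intent. It does not remove the gap, because no section says the deviation is absolute and the model assignment omits it.

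**The hypothesis is tested elsewhere.** A reader might infer that the trial cannot detect a gain in accuracy. The documents do not support that. Achieving 2-6° is the same as |HKA − 4°| ≤ 2°, in which errors in either direction do not cancel. The trial is sized on this outcome and analyses it by logistic regression. This stands in full and limits the point to the continuous analysis. (The endpoint section gives 0-6° where Study procedures and the sample size give 2-6°; that is a separate inconsistency.)

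**The 5% figure depends on equal means.** Aiming at 4° is not averaging 4° a year later. Preservation of correction is part of the primary outcome, and the Discussion describes drift into varus after a medial cortex fracture in LCW. This stands: the alignment regression gains power as the LCW mean drifts, and mean angle is informative about systematic loss of correction. It is still a test of mean shift, and step 6 shows that it can reject when accuracy is equal.

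**Conclusion.** The point holds for the continuous primary analysis only. As worded, that analysis names alignment, omits the deviation from 4° and leaves its sign undefined. Read as the angle or as a signed deviation, it does not measure the hypothesised quantity. Its power against a pure difference in scatter is about 5%, compared with about 93% for the absolute deviation on the same patients. With an LCW mean of 3.5° to 2.5° its power ranges from about 25% to 99.8%, while the absolute deviation stays at 92-93%.

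These figures rest on normality, on SDs back-calculated from the 60% and 85% success rates, and on 50 analysed per arm. The direction of the point does not depend on them: a difference in mean angle is not a difference in closeness to 4°.

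**What to change.** In Main study parameter/endpoint and Study procedures, define the continuous accuracy outcome as the absolute deviation |HKA − 4°| at one year. In Statistics, name it as the dependent variable of the linear regression. Keep the mean HKA (or signed deviation) and its SD per arm as descriptive measures, so that systematic under- or overcorrection can be told apart from scatter. Robust standard errors are optional: the absolute deviation is skewed and its spread would differ between arms in the planning scenario.

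The cost is about one line of wording. No new data, visits or patients are needed, and the sample size is unaffected because it rests on the 2-6° outcome. The choice should be fixed before outcome data are seen, since the two definitions can lead to different conclusions.

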#### Combined wedge osteotomy (CWO)

For the combined wedge HTO, instrumentation of Allopro (Zimmer; Winterthur, Switzerland) will be used. The common peroneal nerve will be exposed and snared with a nerve band. Next, the anterior part of the proximal fibular head (anterior part of the proximal tibiofibular syndesmosis) will be resected. The proximal osteotomy is performed using an oscillating saw up to the center of the tibial head, 2 cm distally from the joint line. After positioning the aiming device in the first osteotomy, a second distal osteotomy is made, which results in a laterally-based bone wedge. The bone wedge is removed. The distal part of the tibia is placed in valgus position, so the lateral part of the osteotomy closes and the medial part of the osteotomy opens. The center of the valgisation is the center of the tibial head. The half bone wedge is placed back in the gap opened on the medial side. The osteotomy is secured with staples, two on the lateral side and one on the medial side. At the end of the procedure a fasciotomy of the anterior compartment will be performed to prevent compartment syndrome.

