### Secondary study parameters/endpoints

Secondary outcome measures are anatomical changes due to HTO and pain and function scores. Parameters are tibial slope (Moore-Harvey and Dejour-Bonin); patellar height (Insall-Salvati and Caton Index) and difference in leg length (cm) one year after surgery; and pain severity (VAS; range 0–10), knee function and quality of life (KOOS), and walking distance (km) at six weeks, three months, six months and one year after surgery.

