## Discussion

Although HTO remains quite successful after 10 years, OA with associated symptoms will progress. Some patients may require total knee replacement (TKR) [15]. Success of TKR for knee OA is well-established, and about 85% of patients are satisfied with the surgical outcome [16], therefore when considering HTO in the early treatment of symptomatic medial compartmental OA subsequent TKA should not be compromised. A randomized clinical trial showed significantly more patellar descent and tibial slope increase after MOW compared to the LCW technique [17]. This may cause exposure and patellar eversion problems during knee replacement that may compromise precision and accuracy of TKR [18]. The advantage of MOW is preservation of bone stock with tensioning of the medial collateral ligament. This may result in a more conservative amount of bone removed during knee joint replacement, so joint line elevation by using a thicker-than-desired tibial component in balancing the ligaments is less likely. Furthermore, unlike LCW, the relative position of the medullary canal is not altered. This may facilitate tibial component placement with intramedullary guidance.

An operative complication that may result in an adverse effect is intraoperative fracturing of the opposite cortex. Avoidance of opposite cortex fracture can be difficult though, and is generally limited by the angular size of the wedge. Opposite cortical fracture occurs often during the LCW technique [15]. A fractured medial cortex in LCW may lead to progressive movement of the distal tibia into a varus position [19]. In case of the MOW, instability at the MOW site due to disruption of the lateral cortical hinge potentially results in displacement of the osteotomy and may contribute to recurrent varus deformity [20]. Newer angular stable plate systems with locking screws seem to avoid this problem. Loss of correction may lead to a suboptimal result [11,21,22]. Still, HTO is considered a very successful surgical procedure with low complication rates. For instance, non-union in HTO is very rare, especially in LCW, and delayed union is seen in about 3-4% [23,24].

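### The hypothesis is about how much the anatomy changes, but the planned regression compares one-year levels without each measure's own preoperative value

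*Protocol article*

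**What the plan says.** The Background (and the abstract) of the protocol article states a two-part hypothesis for CWO: "more accurate overcorrection of varus malalignment with fewer anatomical changes of the proximal tibia after one year". The section on secondary endpoints uses the same idea: "Secondary outcome measures are anatomical changes due to HTO and pain and function scores".

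The measures themselves are then given as levels. That section and Study procedures list tibial slope by two methods, patellar height by two indices, and leg length, all one year after surgery (for example "difference in leg length (cm) one year after surgery will be obtained"). The Statistics section uses multivariable linear regression for "the impact of LCW versus CWO HTO on postoperative alignment, posterior tibial slope, patellar height, leg length", and the list ends with "walking distance and patients with adverse events at the one-year follow-up".

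The possible confounders include "Gender, age and baseline values for HKA angle, VAS knee, KOOS, walking distance, medial osteoarthritis more than joint space loss alone" and concurrent lateral osteoarthritis. The preoperative values of slope, patellar height and leg length are not among them. For alignment, by contrast, the article names a distance measure, the deviation from the 4° target.

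**The concern.** A claim that one technique changes the anatomy less needs a starting point for each knee. The planned model has none for these three measures. Its coefficient says which arm has the higher mean slope, patellar height or leg length at one year. It does not say how far either arm moved from its preoperative state.

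Two things are at stake. First, the second half of the stated hypothesis would rest on a contrast that cannot by itself confirm or refute it. Second, the spread between patients that existed before surgery stays in the error term, so real differences are harder to detect.

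**Working it through.** **Inputs.** The article gives 50 per arm and α = 0.05 (taken as two-sided). It gives no SDs or expected shifts for slope, patellar height or leg length. Assumed here for slope: preoperative SD 3° (range 2° to 4°), change SD 2°, change independent of the preoperative value.

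**The plan's own figure.** For 60% versus 85% success with 80% power, the pooled-variance formula without continuity correction gives 49 per arm, and power at 50 per arm is 80.9%. The stated 50 is reproduced. It concerns the primary outcome and supplies only the n used below.

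**1. What the coefficient cannot show.** Randomisation makes the expected preoperative means equal, so the expected difference in one-year means equals the difference in mean signed change. Three different pairs of mean changes (LCW, CWO) give the same 2° contrast. The mean absolute change is the folded-normal mean with SD 2°:

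| Mean change LCW, CWO | Contrast | Mean absolute change LCW, CWO | Which changed less |
|---|---|---|---|
| -3°, -1° | 2° | 3.12°, 1.79° | CWO |
| -1°, +1° | 2° | 1.79°, 1.79° | neither |
| +1°, +3° | 2° | 1.79°, 3.12° | LCW |

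The planned model returns the same expected coefficient, with the same power, in all three rows.

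**2. Precision.** SD of the one-year value = √(3² + 2²) = √13 = 3.61°.

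- One-year value: SE = 3.61 × √(2/50) = 0.721°; 2/0.721 = 2.77; power about 78%.
- Change: SE = 2 × √(2/50) = 0.400°; 2/0.400 = 5.0; power over 99%.
- Variance ratio = 13/4 = 3.25.

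With a preoperative SD of 2° the one-year value has about 94% power, and with 4° about 60%. The change stays above 99%.

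**3. Would absolute change be a better sole test?** Simulated rejection rates with 50 per arm, preoperative SD 3°, and change SD 2° unless stated:

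| Mean change LCW, CWO | One-year value | Signed change | Absolute change |
|---|---|---|---|
| -1°, +1° | 78% | over 99% | 5% |
| 0°, 0° (change SD 3° and 1.5°) | 5% | 5% | 99% |
| -3°, -1° | 78% | over 99% | 99% |
| -2°, 0° | 78% | over 99% | 73% |
| -1°, 0° | 28% | 70% | 11% |
| -2°, -1° | 28% | 70% | 44% |

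Absolute change is informative when the arms differ in scatter or move in opposite directions. It is weak when CWO leaves the mean unchanged and LCW shifts it modestly, which is a natural form of the hypothesis.

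**The case against.** The strongest reply is that the Statistics list is shorthand. It names postoperative alignment although a deviation from target is defined elsewhere, and it places patients with adverse events among linear-regression outcomes. The endpoint is called anatomical change, and its derivation might sit in an analysis plan that is not shown. This softens the criticism but does not remove it. The article fixes the outcomes, time point, model and candidate covariates, and nothing in those choices refers to the preoperative state of slope or patellar height. Only the leg-length difference could be read as a change, and the text does not say whether it is between legs or over time.

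It is also fair to say that direction matters. The Discussion cites "significantly more patellar descent and tibial slope increase after MOW compared to the LCW technique" as a possible difficulty for later knee replacement. Where both techniques move a measure the same way, as the article suggests for patellar tendon shortening, a signed contrast ranks the arms correctly once the direction is known. This stands, and it is why signed change should stay the main analysis.

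A reader might go further and infer that CWO and LCW will move slope or patellar height in opposite directions, so that equal disturbance would be declared a benefit. The documents do not support that. The cited comparison is of the medial opening wedge with LCW, and the opening wedge is not an arm of this trial. It reports a between-group difference, not opposite directions. That in CWO "the lateral part of the osteotomy closes and the medial part of the osteotomy opens" does not give the sign of any change relative to LCW. Nor does the article say that a significant coefficient alone will count as fewer changes.

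**Conclusion.** The point holds in a limited form. The hypothesis and the endpoint name concern change, while the planned regression compares one-year levels without their own preoperative values. The estimate is not biased; it is incomplete, because it cannot show which arm changed less, and it is imprecise.

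Under the assumed SDs, power for a 2° difference in mean change falls from over 99% to about 78% (60% to 94% for preoperative SDs of 4° to 2°). These figures depend on assumptions the article does not supply. The gain from using the preoperative value shrinks if it correlates less with the one-year value than assumed here (3/3.61 = 0.83).

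A reader might also infer that absolute change should replace the signed analysis. That does not follow: at mean changes of -1° and 0° it rejects in about 11% of trials against about 70% for signed change, and it discards the direction that the Discussion treats as relevant. The primary outcome and the sample size are untouched.

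**What to change.** In the Statistics section:

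- For tibial slope (both methods), each patellar height index and leg-length difference, derive one-year minus preoperative value for each patient.
- Compare arms by linear regression with that measure's preoperative value always in the model, not subject to the 10% rule. With this covariate included, analysing the change or the one-year value gives the same treatment coefficient.
- Report the mean signed change within each arm with its confidence interval. State that a significant contrast is read as fewer changes only if the CWO change is the smaller one.
- Add the between-arm comparison of absolute change as a pre-specified supplementary analysis of the amount of change.
- Say what the leg-length difference is measured against.

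The cost is reading the same indices on preoperative films (assumed available; a preoperative visit is planned), plus a few sentences of analysis text and slightly more reporting. No additional patients are needed.

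### The one-year comparisons of tibial slope, patellar height and leg length leave out each outcome's own preoperative value, so the test of the anatomical half of the hypothesis is less precise than it could be

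*Protocol article*

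**What the plan says.** The Background section of the protocol article gives a two-part hypothesis for the combined wedge technique: "more accurate overcorrection of varus malalignment with fewer anatomical changes of the proximal tibia after one year". Under Secondary study parameters/endpoints the same idea returns as an endpoint: "Secondary outcome measures are anatomical changes due to HTO and pain and function scores".

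The timing given for these parameters is one year. Study procedures lists posterior tibial slope by two methods and then "patellar height (Insall-Salvati and Caton Index) and difference in leg length (cm) one year after surgery will be obtained". That section includes a preoperative visit, but no section mentions a preoperative reading of slope, patellar height or leg length.

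The Statistics section takes as dependent variables postoperative alignment and "posterior tibial slope, patellar height, leg length, VAS, KOOS, walking distance and patients with adverse events at the one-year follow-up". Its possible confounders are "Gender, age and baseline values for HKA angle, VAS knee, KOOS, walking distance, medial osteoarthritis more than joint space loss alone" and concurrent osteoarthritis of the lateral compartment. These variables "are included in the regression models only if they change the relationship between dependent variable and type of HTO by at least 10" per cent.

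**The concern.** The hypothesis is about what the operation does to the proximal tibia, so the natural reference for each patient is that patient's anatomy before surgery. The stated model has no such reference for slope, patellar height or leg length, although alignment, VAS, KOOS and walking distance each have their own baseline among the candidates.

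If patients differ in anatomy before surgery and that difference persists to one year, it enters the comparison as noise. The test of the second half of the hypothesis is then weaker than 100 evaluable patients allow. An accidental difference in preoperative slope or patellar height between the arms would also pass uncorrected into the result.

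**Working it through.** **1. The plan's own figure.** The Sample size calculation section rests on an "expected increase of the success rate from 60% in the closed wedge HTO to 85% in the combined wedge HTO", with α = 0.05 and 80% power, and states 50 per group. The two-sided formula with pooled variance and no continuity correction is

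n = [1.96·√(2·p̄·(1−p̄)) + 0.842·√(p₁(1−p₁) + p₂(1−p₂))]² / (p₂−p₁)²

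With p₁ = 0.60, p₂ = 0.85 and p̄ = 0.725:

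n = [1.96·√0.39875 + 0.842·√0.3675]² / 0.0625 ≈ 48.9, so 49 per arm.

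The stated 50 is reproduced, and gives 80.9% power. It concerns alignment success, so nothing below alters it.

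**2. Does leaving out the baseline bias the contrast?** Allocation is random and equal. Write a one-year value as preoperative value plus change. The expected preoperative value μ₀ is the same in both arms, so

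E(one-year, CWO) − E(one-year, LCW) = [μ₀ + E(change, CWO)] − [μ₀ + E(change, LCW)] = E(change, CWO) − E(change, LCW).

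There is no bias. What remains is precision and chance imbalance.

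**3. How much precision?** Let r be the correlation between the preoperative and the one-year value of the same outcome. The article gives neither r nor an SD for these outcomes, so r is an assumption and effects are in SD units. With the baseline in the model, the residual variance is multiplied by 1−r², and the equivalent sample by 1/(1−r²). At 50 per arm, two-sided 0.05 and 80% power, the detectable difference on one-year values alone is

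(1.96 + 0.842)·√(2/50) = 0.560 SD,

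and with adjustment it is 0.560·√(1−r²). Power is for a true difference of 0.5 SD.

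| Assumed r | Variance factor 1−r² | Equivalent sample | Detectable difference (SD) | Power |
|---|---|---|---|---|
| No baseline in model | 1 | 1 | 0.560 | 70.5% |
| 0.3 | 0.91 | 1.10 | 0.535 | 74.6% |
| 0.5 | 0.75 | 1.33 | 0.485 | 82.3% |
| 0.6 | 0.64 | 1.56 | 0.448 | 87.8% |
| 0.7 | 0.51 | 1.96 | 0.400 | 93.8% |
| 0.8 | 0.36 | 2.78 | 0.336 | 98.6% |

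**4. Would simple change scores do as well?** Their SD is multiplied by √(2(1−r)). For the same 0.5 SD difference, power is 56.1% at r = 0.3, 70.5% at 0.5, 79.8% at 0.6, 89.8% at 0.7 and 97.7% at 0.8. Change scores beat one-year values only if r exceeds 0.5, and are below covariate adjustment at every r shown.

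**5. Would it be enough to add the baselines to the list?** Not under the 10% rule. That rule selects on movement of the treatment estimate, not on how well the covariate predicts the outcome. In a simulation of 20,000 trials per setting (50 per arm, true difference 0.5 SD), it would admit the baseline in about 61% of trials at r = 0.5, 72% at 0.7 and 76% at 0.8.

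**The case against.** A reader might infer that the analysis does not estimate change at all, and so answers a different question from the hypothesis. The article does not support that. By step 2 of the working, the expected difference in one-year values is the expected difference in mean change.

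The strongest case on the other side has four further parts.

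- **The outcomes may already be changes.** The endpoint is worded as anatomical changes, and leg length is given as a difference in centimetres, which the Statistics section shortens to leg length. A stated time point does not settle whether a variable is a level or a change. This stands as an ambiguity. For leg length, a pre-post difference would already be a change score, and the point would weaken for that outcome. Slope and patellar height have no such wording of their own, and no section defines a change score for them.
- **The covariate list may not be complete.** It is introduced as possible confounders, and Other study parameters names more, such as BMI and opposite cortex fractures. It would therefore be wrong to call the list closed. Still, the article names the own baselines of the other continuous outcomes in that sentence's model and omits these.
- **The gain rests on an undocumented correlation.** This stands. Nothing in the article says that these measures track strongly within a person, and the osteotomy may itself alter slope and patellar height. At r = 0.3 the gain is slight.
- **The reach is limited.** This also stands. These are secondary outcomes with no power claim attached.

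**Conclusion.** The point holds as one of precision and clarity, and the change is a cheap improvement. As written, slope, patellar height and leg length at one year are compared without their own preoperative values, although they carry the second half of the hypothesis. The contrast is unbiased under randomisation, but less precise than it need be and exposed to chance baseline imbalance.

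The loss runs from minor to substantial: a variance factor of 0.91 at r = 0.3 and 0.36 at r = 0.8. That range is an assumption, applied alike to three outcomes that may differ in r. The power figures also assume 50 analysed per arm and a difference of 0.5 SD, which the article does not state. The primary outcome and the planned 110 patients are untouched.

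**What to change.** In Study procedures, state that tibial slope (both methods), patellar height (both indices) and leg-length difference are read preoperatively by the same methods as at one year. For leg length, first define whether the difference is side-to-side or pre-post.

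In Statistics, always include each outcome's own preoperative value as a covariate in its one-year model (ANCOVA), exempt from the 10% change-in-estimate rule. With that covariate in the model, the technique coefficient is the same whether the dependent variable is the one-year value or the change from it, so the result can be reported as an adjusted difference in change.

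The cost is the work of measuring these parameters on preoperative films. It is small but not nil: an endpoint of anatomical changes implies such readings, but the article does not say that they are made. No change to the primary analysis or the sample size is needed.
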